### Patient and public involvement

The TSC has a patient representative and the patient-facing documents have been reviewed and commented on by the patient representatives.

#### AE reporting

All AEs grade 3 or above on the NAESS/SAE will be reported to CCTU within 24 hours until the participant reaches day 7 following the last administration of the IMP (preclinical studies have demonstrated that the IMP is not detectable in plasma sample taken 24 hours after final administration). All related events that are graded 1 or 2 according to the NAESS will be reported within 7 days. After day 7 any events that are considered related to the IMP will be reported within 24 hours of knowledge to the sponsor. Assessments for and reporting of all AEs related/unrelated will continue until 40 weeks PMA or hospital discharge. All aggregated AEs data will be considered by the DSMB at each meeting to confirm that there are no trends, safety signals or safety concerns. Examples of AEs that are exempt from reporting are those that are graded 1 or graded 2 according to the NAESS criteria if considered not related to the IMP. These are common observations in preterm infants and do not require a change in clinical management unless sustained, that is, grade 3 and above on the NAESS. There is no formal frequency of audit for this study but will be overseen by the sponsor and if required by the Medicine and Healthcare products Regulatory Agency.

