### Dose-limiting events

The severity of all AE and/or adverse reactions (serious and non-serious) in this trial will be graded using the toxicity graded in the NAESS V.1.0.^35^ The NAESS has been developed as existing scores such as the Common Terminology Criteria for Adverse Events is not suitable for use in a study involving neonates. The NAESS developed by the International Neonatal Consortium has been developed to facilitate the conduct and appropriate interpretation of neonatal clinical trials such as RESPONSE.^36^

Grades for neonatal-specific AEs according to the NAESS V.1.0^35^ are:

Grade 1: Mild; asymptomatic or mild symptoms; clinical or diagnostic observations only; no change in baseline age-appropriate behaviours^*^; no change in baseline care or monitoring indicated.

Grade 2: Moderate; resulting in minor changes of baseline age-appropriate behaviour^*^; requiring minor changes in baseline care or monitoring^*+^.

Grade 3: Severe; resulting in major changes of baseline age-appropriate behaviour^*^ or non-life-threatening changes in basal physiological processes^+^ requiring major change in baseline care or monitoring^**_._^

Grade 4: Life-threatening; resulting in life-threatening changes in basal physiological processes^+^; requiring urgent major change in baseline care***.

Grade 5: Death.

*Age-appropriate behaviour refers to oral feeding, voluntary movements and activity, crying pattern, social interactions and perception of pain.

^+^Basal physiological processes refer to oxygenation, ventilation, tissue perfusion, metabolic stability and organ functioning.

**Minor care changes constitute: brief, local, non-invasive or symptomatic treatments.

*** Major care change constitute: surgery, the addition of long-term treatment and upscaling care level.

The DSMB will determine the occurrence of a DLE based on the following criteria:

A single event defined as grade 3 or above on the NAESS that is possibly, probably or definitely thought to be related to the IMP. Relatedness will be confirmed by an independent neonatologist at the participating site.A single serious AE (SAE) that is possibly, probably or definitely thought to be related to the IMP. Relatedness will be confirmed by an independent neonatologist at the participating site.Concerns over frequency of any AEs reported at grade 2 on the NAESS that are possibly, probably or definitely thought to be related to the IMP.

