### Sample size and statistical analysis

As this is a safety study, no formal sample size calculation has been performed. A sample size of 24 infants is planned to meet practical recruitment and time targets and to collect sufficient data to quantify the estimated risk of DLE at each dose level. Participants with unclear safety outcomes or who have not started study treatment will be replaced to meet our planned effective sample size of 24 participants.

The primary outcome of interest is the occurrence of DLEs at the dose levels under investigation and the identification of the dose(s) that, for infants of particular risk profiles defined by GA, have an estimated risk of DLE closest to the target side effect level of no greater than 20%. The use of Bayesian methodology to estimate risks will allow information to be borrowed across dose levels, making the dose-escalation and RP2D identification procedure more efficient than a standard rule-based approach.

The operating characteristics of the design, for three specific scenarios, are shown in table 3. The first scenario is one where the initial a priori DLE probabilities calculated by calibration (halfwidth of the indifference interval set at 0.05) correspond to the true underlying probabilities of DLE. The second scenario is such that the true DLE rate of the second dose level corresponds to the target DLE rate. The third scenario is one where the true probabilities are much lower than the a priori probabilities.

Type and grade of DLEs, SAEs and AEs will be tabulated per dose level, and further summarised by risk group defined by GA. Mean estimated risk of DLE per dose level and 95% credibility intervals will be calculated using the study model. Secondary objectives will be described per dose level and risk category. Categorical variables will be summarised by frequencies and percentages, and continuous variables by means/medians and SD/IQRs per dose level.

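### The reason given for not reporting unrelated grade 2 events contradicts the protocol's own grade 2 definition, and the exemption conflicts with its statements on all-AE reporting, tabulation and DSMB review

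*Protocol article*

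**What the plan says.** Four parts of the protocol article bear on this.

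- **AE reporting, exemption.** Exempt events include "those that are graded 1 or graded 2 according to the NAESS criteria if considered not related to the IMP". The justification is that these are common in preterm infants and "do not require a change in clinical management unless sustained, that is, grade 3 and above on the NAESS".
- **AE reporting, general rule.** The same section says: "Assessments for and reporting of all AEs related/unrelated will continue until 40 weeks PMA or hospital discharge". It also has the DSMB look at aggregated adverse event data at each meeting to confirm that there is no trend or safety signal. Related grade 1 and 2 events have their own reporting limit of 7 days.
- **Dose-limiting events.** Grade 1 means "no change in baseline care or monitoring indicated". Grade 2 means an event "requiring minor changes in baseline care or monitoring", and the footnote explains minor care changes as brief, local, non-invasive or symptomatic treatment. The third route to a dose-limiting event is concern over how often grade 2 events related to the study drug occur.
- **Sample size and statistical analysis; Interim analyses of DLEs.** "Type and grade of DLEs, SAEs and AEs will be tabulated per dose level", with no restriction to related events. The interim section has the DSMB review all NAESS data after each of the first three infants at a dose level, and all clinical data with each later cohort of three.

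**The concern.** The exemption rests on a factual premise, that the exempted events change nothing in management. The protocol's own grading makes that untrue for grade 2. If the premise fails, so does the case for treating unrelated grade 2 events like unrelated grade 1 events.

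The statistical stake is which grade 2 events enter the data. Where moderate events are common in the background population, judging causality infant by infant is difficult. The natural complement is to compare rates of all such events, whatever their attributed cause, across the three dose levels. That comparison needs unrelated events to be in the data. If they are filtered out by attribution before tabulation, neither the final table nor the aggregated data given to the DSMB can support it, and nobody downstream can reconsider the attribution. This matters more than usual in a first-in-human study without a randomised control, whose primary purpose is the safety profile by dose.

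**Working it through.** No arithmetic applies. The plan states no figure on this point and gives no grade 2 event rate, so the check sets the statements side by side.

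1. **Reason against definition.** The exemption says that the events need no management change. Grade 1 is defined by no change in care or monitoring, so the reason holds for grade 1. Grade 2 is defined by a minor change in care or monitoring, and the footnote makes a minor care change a treatment. The reason is therefore contradicted for grade 2.

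2. **The word sustained.** The justification equates a sustained event with grade 3 and above. The grade definitions separate grades 2 and 3 by severity and by the size of the care change, not by duration. A persistent grade 2 event stays grade 2 on those definitions, and would stay exempt if considered unrelated.

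3. **Exemption against the other statements.** There are three possible readings.
   - *The exemption is literal.* Unrelated grade 2 events are not reported. This conflicts with the all-AE sentence in the same section, with DSMB review of all NAESS data, and with a dose-level table of AE type and grade that has no relatedness limit.
   - *The all-AE sentence governs.* Everything is reported, and the exemption has no effect.
   - *The exemption covers notification to the trials unit only.* The events are still recorded, tabulated and reviewed. The statements then agree, but the article does not say this. The section already gives related grade 1 and 2 events a slower 7-day route, so reporting there means more than 24-hour notification.

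   The text does not say which reading applies.

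4. **Consequence of the literal reading.** The grade 2 rows of the dose-level table, and the grade 2 part of the aggregated data seen by the DSMB, would hold only events judged related. All-causality grade 2 rates at 1, 2 and 4 mg/kg could not be formed.

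5. **Check on attribution.** The Dose-limiting events section attaches confirmation of relatedness by an independent neonatologist to the grade 3-or-above criterion and to the SAE criterion. It does not attach it to the grade 2 frequency criterion. The data collection section mentions independent causality assessment for dose-limiting events. An unrelated grade 2 event that is never reported would not get that far.

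6. **Capture already planned.** AE review is marked at four time points in Table 1 (baseline and before each of the three instillations). It is marked in all eight columns of Table 2, one of which covers days 14, 21 and 28, so 7 + 3 = 10 time points. In total 4 + 10 = 14 reviews per infant are already scheduled, whatever the attribution.

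**The case against.** The strongest reply is that reporting is not recording. The section's time limits concern notification to the trials unit or sponsor, the exempt events are introduced only as examples, and a journal article condenses a fuller protocol that may say that all events are logged. That may well be the intent, and the point does not rest on missing detail. It rests on a stated reason that a stated definition contradicts, and on statements that cannot all be followed literally.

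A second reply is that the all-AE sentence mainly fixes duration, with the exemption as a carve-out from it. That would soften one conflict. It would leave the mismatch with the grade 2 definition, the unrestricted dose-level table and the DSMB's access to all NAESS data.

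Several stronger readings are tempting, and the documents do not support them.

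- *The DSMB cannot see unattributed moderate harm.* This is not established. The dose escalation, interim analysis and AE reporting sections promise it all safety data, all NAESS data and aggregated AE data. Vital signs, oxygen concentration, ventilator settings and cranial ultrasound are also collected on schedule regardless of attribution.
- *The data would be biased towards showing no dose trend.* The direction is unknown. In an open-label escalation, assessors might attribute more events at higher doses, which would exaggerate a trend.
- *The treating site makes the judgement.* The exemption says only that the event is considered unrelated and names no assessor.
- *A numerical loss of signal can be stated.* It would need assumed background rates, drug effects and attribution rates, none of which the article gives. With 24 infants, even complete all-causality data would support only a descriptive comparison.
- *The primary analysis is compromised.* The grade 2 dose-limiting criterion counts related events only. The dose-escalation model is affected only if a truly related grade 2 event is misattributed.

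**Conclusion.** The point holds as an internal contradiction with a conditional consequence. The contradiction is certain on the text: the reason for exempting unrelated grade 2 events is incompatible with the definition of grade 2, and the exemption taken literally is incompatible with the all-AE reporting sentence, the DSMB review of all NAESS data and the dose-level AE table.

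The consequence depends on the exemption being followed as written. In that case grade 2 data are filtered by attribution before they reach the table and the aggregated DSMB data, all-causality comparison across doses is lost for that grade, and an initial judgement of unrelated cannot be revisited. If the exemption was meant to cover notification only, the data are intact, and what remains is an incorrect rationale and an unclear instruction.

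No size can be given. The point should be corrected because the safety profile by dose is the trial's primary purpose and the correction is cheap. It does not invalidate the design or the primary model.

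**What to change.** Reconcile the AE reporting, Dose-limiting events, Sample size and statistical analysis, and Interim analyses of DLEs sections.

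1. In AE reporting, either limit the exemption to grade 1 events considered unrelated, or state that for grade 2 it covers notification to the trials unit only. Remove or correct the rationale so that it no longer describes grade 2 events as needing no change in management, or grade 3 as a sustained lower grade.
2. State that grade 2 events of any causality are recorded at the AE reviews already scheduled in Tables 1 and 2, without expedited reporting.
3. In the statistical section, state that events of grade 2 and above are tabulated per dose level twice, once for all causes and once for those judged related. Supply both tables for the final analysis and at each DSMB meeting.

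The cost is protocol wording and some extra data entry for 24 inpatients at reviews already planned. The downside is a longer AE listing containing many background events. No dose, stopping rule or treatment is changed.

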### Significance of study

Despite the medical advances in neonatal medicine, the incidence of BPD has not changed over the years, and one may argue that it has increased because we see an increasing number of extremely preterm infants survive to discharge. The lifelong morbidity associated with BPD has significant implications for healthcare systems around the world.

Infants at the highest risk of BPD are born at a GA when the majority of the alveolar and vascular development in the lungs occurs. Immaturity of the lungs means they have a developmental deficiency of surfactant leading to RDS. Ongoing lung injury secondary to postnatal insults such as infection and mechanical ventilation leads to ongoing interruption to lung development. Efforts have been made over the years to reduce these insults by changes in ventilation strategies, early nutrition and proactive management of infection in the hope that the lungs will repair and remodelling will lead to recovery of the lung parenchyma. However, a significant number of preterm infants will have multiple insults and despite best efforts will have abnormal repair with little lung recovery leading to BPD. Inflammation remains at the centre of the pathophysiology of BPD and the most promising target for therapies. Given this, there is a need for novel anti-inflammatory therapies to be explored such as SP-D.

The role of SP-D in lung immune homeostasis is well established but due to its propensity to oligomerise does not lend itself well to a stable drug form. The proposed recombinant fragment of SP-D has been developed into a stable drug form for endotracheal administration and animal studies in a well-established translational model have demonstrated its potential anti-inflammatory effects. This phase I safety study using dose escalation of 1–4 mg/kg will aim to identify a recommended phase 2 dose for a subsequent randomised phase 2 study in preterm infants born at less than 28 weeks gestation who are at the highest risk of developing neonatal chronic lung disease.

## Ethics and dissemination

All results and analyses from the study will be published in peer-reviewed journals and presented at national and international conferences. All data generated in this study will be anonymised and the study will be conducted per Good Clinical practice. Access to the full study protocol will be given on request and participant-level data will only be given if authorised by the sponsor for auditing purposes. Any substantial or non-substantial amendment to the study must be approved by the Health Research Authority and will be communicated with the NHS trust research and development team to ensure site implementation. Any study material that is related to participant information or informed consent will be submitted to the principal research ethics committee for approval. This study has been approved by London-Brent NHS Research Health Authority ethics committee (REC reference 23/LO/0381) and has clinical trials approval (CTA 20363/0453/001-0001) in place.
